### Access to data

All authors of the study protocol will have access to the final and fully anonymized data set.

### Statistical analysis

We analyze the short-term effects (end of rehabilitation and 3-months follow-up) and long-term effects (12-months follow-up) to show non-inferiority of the hybrid rehabilitation program. The results of the short- and long-term effects will be published separately.

To test the primary hypothesis of non-inferiority, the confidence interval method is applied [47, 48]. We determined -4 points as the non-inferiority margin. Four points are slightly below the smallest clinically important difference (5.5 to 8.5 points) reported in a recent systematic review on pain self-efficacy in patients with low back pain [49]. We assume non-inferiority of the hybrid rehabilitation if the lower boundary of the one-sided 95% confidence interval (CI) exceeds -4 points.

The estimate of the treatment effect is adjusted for the baseline scores of the dependent variable, as well as for the treatment center (outpatient rehabilitation center). To estimate group differences for continuous and binary outcome variables, linear or logistic regression is calculated. Regression coefficients or odds ratios and their 95% CI are determined. Confidence intervals are two-sided for all secondary outcomes.

Age, sex, level of education, electronic health literacy, and motivational self-efficacy are considered as moderators of the treatment effect on our primary outcome variable. The interaction effects are assessed through p-values. All secondary outcome variables are tested on superiority of the intervention group, and we present p-values. We test superiority to identify potential group differences that, in the case of non-inferiority, can be used to formulate a preference for one of the two treatments [50].

In order to perform an intention-to-treat analysis, missing values are imputed by multiple imputation using 20 independent data sets [51, 52]. The parameter estimates are combined according to Rubin’s rules [53].

A sensitivity analysis also calculates unadjusted estimates for the intention-to-treat analysis. An additional sensitivity analysis is conducted as complete case analysis. Like in the primary analysis, we adjust for the baseline scores of the dependent variable and for the treatment center. We also conduct a per-protocol analysis, including only individuals in both groups who participated in six of the seven back school modules.

Withdrawal from consent leads to deletion of the participant’s data.

The analyses are performed with Stata 16.1 (StataCorp, College Station, Texas, USA). A two-tailed p-value of less than 0.05 is considered statistically significant.

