## Objectives

We hypothesize that patients receiving the hybrid rehabilitation program achieve as comparable pain self-efficacy as patients receiving the back school within a conventional rehabilitation program. Additional comparable outcomes are expected for other variables. Guided interviews explore the structure and processes of the hybrid rehabilitation program.

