### Outcomes

All outcomes, including measurement points and expected scaling, are shown in Table 3. Since no adverse events are expected, no plans for collecting, assessing, reporting, or managing of adverse events were made.

**Table 3 Tab3:** Measures, assessment, expected scaling, and measurement occasions

Outcome	Source and reference	Scaling	Scoring	Measurement time points			
				**Start of rehabilitation**	**End of rehabilitation**	**3 months follow-up**	**12 months follow-up**

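### Unadjusted superiority tests on about 60 secondary comparisons may be used to prefer one treatment, with no control over false signals

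*Protocol article*

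**What the plan says.** All the statements at issue are in the Statistical analysis section of the protocol article, read with Table 3.

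- Test set: "All secondary outcome variables are tested on superiority of the intervention group, and we present p-values".
- Use: the section explains that superiority is tested to find group differences that, "in the case of non-inferiority, can be used to formulate a preference for one of the two treatments".
- Threshold: "A two-tailed p-value of less than 0.05 is considered statistically significant". No adjustment, testing order or key secondary outcome is attached to it, and the secondary tests are not called exploratory.
- Intervals: "Confidence intervals are two-sided for all secondary outcomes". They are ordinary 95% intervals, not simultaneous ones.
- Time points: effects are analysed at the end of rehabilitation, at 3 months and at 12 months. Short-term and long-term results are published separately.
- Outcomes: "All outcomes, including measurement points and expected scaling, are shown in Table 3".

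**The concern.** Unadjusted secondary tests are usually tolerable because nothing is decided on them. Here the article gives them a role: they may support choosing one treatment over the other after the primary question is settled. That use comes with a large set of outcomes, three post-baseline time points and a fixed 0.05 for every test. With that many tests, some significant differences are expected even if the two forms of back school work equally well. A reader told that hybrid rehabilitation is non-inferior and also better on a particular scale could not tell a real advantage from a chance result.

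**Working it through.** **Inputs.** The per-test level is 0.05 two-sided (Statistical analysis). Outcomes and time points come from Table 3. Correlations between outcomes are not given, so 0, 0.3, 0.5 and 0.7 are assumed.

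**Step 1: count the comparisons.** Only outcomes measured after baseline in both arms are counted.

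| Outcomes in Table 3 | Outcomes × times | All times | At 12 months |
|---|---|---|---|
| Current health, mental health, functional capacity, pain | 4 × 3 | 12 | 4 |
| FESV subscales | 6 × 3 | 18 | 6 |
| Motivational self-efficacy | 1 × 1 | 1 | 0 |
| Knowledge, self-efficacy in practice, eHEALS | 3 × 3 | 9 | 3 |
| Self-informing, two adherence items | 3 × 2 | 6 | 3 |
| Two work ability scores, current sickness absence | 3 × 3 | 9 | 3 |
| Weeks of absence, employment | 2 × 2 | 4 | 2 |
| ZUF-8 | 1 × 1 | 1 | 0 |
| **Total** | | **60** | **21** |

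Without the six ordinal comparisons the total is 54. With the three nominal aftercare items at two time points it is 66.

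**Step 2: false positives when the arms are identical.** The expected number is 60 × 0.05 = 3.0 over all time points and 21 × 0.05 = 1.05 at 12 months. If the tests were independent, the chance of at least one is:

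- 60 tests: 1 − 0.95^60 = 0.954
- 54 tests: 1 − 0.95^54 = 0.937
- 66 tests: 1 − 0.95^66 = 0.966
- 21 tests: 1 − 0.95^21 = 0.659

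**Step 3: allow for correlation.** The test statistics are taken as multivariate normal with mean zero and one common pairwise correlation.

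| Assumed correlation | 60 tests | 21 tests at 12 months |
|---|---|---|
| 0 | 95% | 66% |
| 0.3 | 85% | 56% |
| 0.5 | 66% | 43% |
| 0.7 | 43% | 30% |

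A common correlation across all 60 tests is a strong assumption. If outcomes correlate at the stated value within a time point and less across time points (time correlation 0.5 to 0.7), the 60-test figures are 84–87% at 0.3, 71–76% at 0.5 and 53–59% at 0.7.

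**Step 4: does requiring non-inferiority first protect?** The standard deviation is not printed. The stated minimum of 242 (121 per arm), margin 4, one-sided 5% and power 90% imply 4 × √(121/2) / (1.645 + 1.282) ≈ 10.63. With 160 per arm and that value, identical arms pass the non-inferiority test with probability about 0.957. Under the second correlation structure of step 3, the chance of passing and also having at least one false positive among 60 is 80–84% at 0.3 and 67–72% at 0.5. The condition removes little.

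**The case against.** The strongest reply is that a significant result is not a preference. The wording is permissive ("can be used to formulate a preference for one of the two treatments"), and the article does not say that one significant difference among many is enough. This stands. A reader might infer from the figures that a false preference is likely, but the article does not support that, because it fixes neither a number nor a pattern of results that would make one. Mixed results could also cancel out. With 60 independent tests, false positives in both directions occur with probability 1 − 2 × 0.975^60 + 0.95^60 ≈ 61%. At a common correlation of 0.3 this falls to about 11%, and at 0.5 to about 1%, so it gives little comfort for overlapping questionnaire scales.

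Second, pooling all time points is the widest family. The primary outcome is at 12 months and the two sets of results are published separately, so 21 may be the fairer count. This stands in part: the 12-month figures are given for that reason, but the article does not restrict the preference to 12 months.

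Third, multiplicity is commonly left to an analysis plan. That would answer mere silence. Here the article itself fixes the test set, the per-test level and the use to be made of the results.

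Two further readings go too far. The Objectives say "Additional comparable outcomes are expected for other variables", which might suggest that non-significance will be read as comparability, but no passage says so. And taken literally, testing all secondary outcomes would cover intervention-only and baseline-only items, but Table 3 marks these clearly and a between-arm test of them is evidently not meant.

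**Conclusion.** The concern holds in this form: the plan allows a treatment preference to rest on about 60 unadjusted tests, with no rule for turning significant results into a preference. The chance of at least one false significant difference available for that purpose ranges from about 95% (independence) to 43% (common correlation 0.7) over all time points, and from about 66% to 30% at 12 months alone. The count comes from Table 3. The correlations are assumptions, and independence is an upper bound that related scales will not reach. Even the lowest figure is several times the nominal 5%. The non-inferiority test on pain self-efficacy and its error rate are not affected, so this bears on a supplementary conclusion and not on the trial's main result.

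**What to change.** Three changes of wording suffice, with no new data:

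1. Once non-inferiority is shown, base any preference statement on superiority for 12-month FESS, from the same adjusted model, using the two-sided 95% interval. Because it is tested only after non-inferiority, this step needs no alpha penalty.
2. Report the secondary outcomes as exploratory estimates with 95% intervals, and state that they cannot support a preference on their own.
3. If the sponsor wants some secondary outcomes to carry such a claim, name a short list of 12-month outcomes in advance and control the error over it, for example with Holm's procedure. The choice of outcomes is the sponsor's. Motivational self-efficacy, which the Abstract names first among the secondary outcomes, is not measured at 12 months in Table 3 and so could not be on that list.

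The cost is that fewer outcomes can support a preference, and each listed outcome is tested with less power than at an unadjusted 0.05.

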### Sample size

A difference of four points for pain self-efficacy [25] was determined as the minimum relevant difference between the intervention and control group. The minimum required sample size for our non-inferiority analysis is 242 participants (one-sided error: 5%, power: 90%) to perform an intention-to-treat analysis after multiple imputation. The standard deviation for our sample size calculation was taken from the randomized controlled trial on the effectiveness of the study by Mangels et al. [46]. We are planning to recruit 320 participants from eight outpatient rehabilitation centers (intervention group: *n* = 160; control group: *n* = 160), which result in 20 participants for both arms of the study within each outpatient rehabilitation center. The sample size is sufficient for a secondary analysis including only patients with complete follow-up. The anticipated flow of participants is shown in Fig. 1.

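### With 20 imputations, a borderline non-inferiority verdict can depend on the imputation run; at least 200 would remove most of this noise at almost no cost

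*Protocol article*

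**What the plan says.** The Statistical analysis section of the protocol article fixes three things that meet at this point.

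- Number of imputations: "missing values are imputed by multiple imputation using 20 independent data sets".
- Pooling: "The parameter estimates are combined according to" Rubin's rules.
- Decision: "We determined -4 points as the non-inferiority margin", and the hybrid programme is taken as non-inferior "if the lower boundary of the one-sided 95% confidence interval (CI) exceeds -4 points".

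The Sample size section uses a one-sided error of 5% and power of 90%. It states: "The minimum required sample size for our non-inferiority analysis is 242 participants". It then says: "We are planning to recruit 320 participants from eight outpatient rehabilitation centers", and adds that this number also suffices for an analysis of patients with complete follow-up. The primary time point is 12 months. The questionnaire for it is sent by post with a single reminder (Data collection section), so a fair amount of imputation is foreseeable.

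**The concern.** Multiple imputation draws the missing values at random. With a finite number of sets, both the pooled estimate and the estimated between-imputation variance carry Monte Carlo error, and so does the confidence bound. For a descriptive estimate this hardly matters. Here the bound is compared with a fixed threshold and gives a yes-or-no answer. If it lies close to -4, two analysts who follow the plan faithfully on the same data could report opposite conclusions only because their random numbers differ. That part of the uncertainty comes from the computation and not from the patients, and it can be made as small as one likes. Because the protocol itself fixes the figure of 20, this concerns a stated rule and not a detail left to an analysis plan.

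**Working it through.** **Inputs from the protocol.** Margin 4, one-sided 5%, power 90%, required total 242 (121 per arm), recruited 320 (160 per arm), 20 imputations, Rubin's rules, analysis adjusted for baseline score and center.

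**Inputs that had to be assumed.**
- SD: not printed. Solving the usual formula with a true difference of 0 gives SD = 4 × sqrt(121/2) / (1.645 + 1.282) = 10.63. An SD of 10.6 returns 242; 10.5 gives 238 and 10.7 gives 246. The stated 242 is therefore consistent with an SD near 10.6, but cannot be reproduced forward.
- Loss: no rate in the text. The surplus implies (320 - 242)/320 = 78/320 = 24.4%.
- Baseline correlation r: not stated; 0 to 0.7 is used.

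**Formulas.** Residual variance s² = 10.63² × (1 - r²). Variance with complete data W = 4s²/320. Variance with infinitely many imputations T = 4s²/242. Between-imputation variance B = T - W. Run-to-run SD of the pooled estimate with m sets = sqrt(B/m). This takes the imputation model to add no information beyond the analysis model.

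For r = 0: s² = 113.0, W = 1.413, T = 1.868, B = 0.455, so sqrt(0.455/20) = 0.151. For r = 0.7: s² = 57.6, W = 0.721, T = 0.953, B = 0.232, so sqrt(0.232/20) = 0.108.

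The bound is noisier than the estimate because B is itself estimated from m values. Simulating that (chi-square noise in B with m - 1 degrees of freedom, Rubin's total variance, small-sample degrees of freedom, 400,000 replicates) gives the following at 24.4% loss:

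| r | Sampling SE | SD of bound, 20 sets | SD of bound, 200 sets |
|---|---|---|---|
| 0 | 1.37 | 0.179 | 0.056 |
| 0.3 | 1.30 | 0.172 | 0.053 |
| 0.5 | 1.18 | 0.156 | 0.048 |
| 0.7 | 0.98 | 0.128 | 0.039 |

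**Share of trials in which two runs on the same data disagree on the verdict (24.4% loss, r from 0.7 to 0).**

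| True difference | 20 sets | 200 sets |
|---|---|---|
| 0 | 0.3% to 2.7% | 0.1% to 0.8% |
| -2 | 5.5% to 5.9% | 1.7% to 1.8% |

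**Operating characteristics.** At a true difference of -4 the rejection rate is about 5% with 20 sets and with infinitely many. At a true difference of 0 and r = 0, power is 89.5% with 20 sets against 89.9% with infinitely many.

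**Cross-check.** A full simulation with proper regression imputation from arm, baseline (r = 0.5) and the 3-month score (r = 0.5 to 0.65) gave a run-to-run SD of 0.13 to 0.15 at 24% loss. This is slightly below the 0.156 above, as expected when a follow-up score helps the imputation.

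**The case against.** The strongest reply is that nothing here is invalid. Rubin's rules already include the term for a finite number of sets, so the error rate is kept. The noise of 0.13 to 0.18 points sits beside a sampling SE of about 1 to 1.4 points, and most trials would not be affected. The planned complete-case analysis carries no imputation noise and would be read alongside a close result. The SD, loss and correlation are all inferred or assumed, and Fig. 1, which may show a planned loss, is not available. FESS is also measured at the end of rehabilitation; an imputation model using it could lower the noise further. All of this stands, and it keeps the point small.

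It does not remove the point. The complete-case analysis is a sensitivity analysis and does not decide the verdict. The decision rests on the imputed bound, and the number of sets behind it is fixed at 20.

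Some stronger readings are tempting but not supported:
- A reader might put the noise at 0.20 points under the loss that the plan covers. At 24.4% loss the maximum is 0.18, and only with no baseline correlation; 0.20 needs about 30% loss or more with a weak correlation.
- A reader might say that 20 sets widen the interval for no reason. The widening is the correct allowance for a finite number of sets and is tiny: for r = 0, (0.455/20)/1.868 = 1.2% of the variance, or about 0.01 points on the bound.
- A reader might fault the absence of a seed or of a full imputation model. Both commonly belong in the analysis plan, which is not shown.

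**Conclusion.** The point holds as a minor, nearly free improvement. With 20 imputations and about 24% loss, the deciding bound varies between runs with an SD of about 0.13 to 0.18 points. A result within roughly 0.2 to 0.4 points of -4 could change verdict on a rerun. The effect is largest when the true difference lies part-way to the margin (about 6% of trials at -2) and small if the arms are truly equal (at most 2.7%).

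It should not be read as showing that the primary analysis is biased, that it inflates the type I error or that it is underpowered: the error rate stays near 5%, and the power loss at a true difference of 0 is under half a percentage point. Nor does the protocol contradict itself here. The figures rest on the back-solved SD, the inferred loss and the assumed range of correlations; a higher loss would raise them, and a more informative imputation model would lower them.

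**What to change.** In the Statistical analysis section, replace 20 with at least 200 imputations for the primary outcome. Add that the Monte Carlo error of the lower bound will be reported, and that sets will be added if it exceeds a pre-set limit, for example 0.05 points. The top-up clause matters: in the least favourable case above (r = 0), 200 sets give about 0.055, and since the noise falls with 1/sqrt(m), about 200 × (0.055/0.05)² = 242 sets would be needed to meet that limit.

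A small amount of disagreement between runs remains with any finite number of sets, but it would drop to about 0.1% to 0.8% of trials at a true difference of 0 and to under 2% at -2. The cost is a few minutes of computing, with no effect on patients, sample size or design.

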## Discussion

Our randomized controlled trial compares a hybrid rehabilitation that implements an online back school with a rehabilitation that conventionally provides a face-to-face back school. We aim to demonstrate non-inferiority of the hybrid rehabilitation. All findings of this study will be published in peer-reviewed journals and presented at conferences. The authors of this present study protocol will also write the publication of the findings. No professional writers will be included in the process.

The SPIRIT checklist (Standard Protocol Items: Recommendations for Interventional Trials) was used when drafting the study protocol [54].

### Trial status

Recruitment has started and is still ongoing.

## Data Availability

The datasets used and/or analyzed during the current study are available from the corresponding author on reasonable request.

## Abbreviations

FESS: Pain Self-Efficacy Questionnaire (German: Fragebogen zur Erfassung der schmerzspezifischen Selbstwirksamkeit)
COPSOQ: Copenhagen Psychosocial Questionnaire
IRES-24: Indicators of Rehabilitation Status (German: Indikatoren des Rehastatus)
FESV: Questionnaire for the Assessment of Pain Processing (German: Fragebogen zur Erfassung der Schmerzverarbeitung)
eHEALS: EHealth Literacy Scale
ZUF-8: Client Satisfaction Questionnaire (German: Fragebogen zur Messung der Patientenzufriedenheit)
SUS: System Usability Scale
SPIRIT: Standard Protocol Items: Recommendations for Interventional Trials
TIDieR: Template for Intervention Description and Replication
HCP: Health care professional
